## Abstract

**Background:**

Freezing of gait (FOG) is a particularly debilitating motor deficit seen in a subset of Parkinson’s disease (PD) patients that is poorly responsive to standard levodopa therapy or deep brain stimulation (DBS) of established PD targets such as the subthalamic nucleus and the globus pallidus interna. The proposal of a DBS target in the midbrain, known as the pedunculopontine nucleus (PPN) to address FOG, was based on its observed pathology in PD and its hypothesized involvement in locomotor control as a part of the mesencephalic locomotor region, a functionally defined area of the midbrain that elicits locomotion in both intact animals and decerebrate animal preparations with electrical stimulation. Initial reports of PPN DBS were met with much enthusiasm; however, subsequent studies produced mixed results, and recent meta-analysis results have been far less convincing than initially expected. A closer review of the extensive mesencephalic locomotor region (MLR) preclinical literature, including recent optogenetics studies, strongly suggests that the closely related cuneiform nucleus (CnF), just dorsal to the PPN, may be a superior target to promote gait initiation.

**Methods:**

We will conduct a prospective, open-label, single-arm pilot study to assess safety and feasibility of CnF DBS in PD patients with levodopa-refractory FOG. Four patients will receive CnF DBS and have gait assessments with and without DBS during a 6-month follow-up.

**Discussion:**

This paper presents the study design and rationale for a pilot study investigating a novel DBS target for gait dysfunction, including targeting considerations. This pilot study is intended to support future larger scale clinical trials investigating this target.

**Trial registration:**

ClinicalTrials.gov identifier: NCT04218526 (registered January 6, 2020)

## Background and rationale

### Refractory freezing of gait in Parkinson’s disease

Gait dysfunction is a common and heterogeneous feature of Parkinson’s disease (PD), significantly impacting patients’ quality of life and increasing their risk for falls [1]. Common characteristics of parkinsonian gait include decreased stride length, reduced arm swing amplitude, and a flexed and stiffened trunk posture [2]. Some of these aspects of gait are improved with dopaminergic therapy or deep brain stimulation (DBS) of conventional targets such as the subthalamic nucleus (STN) or globus pallidus interna (GPi) [3]. Other deficits, such as postural instability and freezing of gait (FOG), may not respond or even worsen [4].

FOG is considered the most disabling of these gait deficits and is described as the transient and episodic failure to move forwards, despite intending to walk [5]. Patients describe feeling as if their feet are “glued” to the floor, and these episodes result in significantly decreased quality of life and contribute to falls and their related morbidities [6–8]. FOG is triggered in situations that highlight both cognitive and sensory influences on gait: during attempts to initiate stepping or turning, when navigating narrow corridors and obstacles, and when the patient is distracted or under duress [9, 10]. Conversely, these episodes frequently improve or resolve with the help of auditory or visual cues, such as a metronome set to a step cadence, or lines marked on the floor set to a desired stride length [11].

The pathophysiology of FOG is incompletely understood, but observations that it can be refractory to dopaminergic therapy suggest that it involves both dopaminergic and non-dopaminergic mechanisms [12]. FOG is associated with advanced PD [13], though it can present early [11]. While some controversy remains as to whether severe gait difficulties represent a distinct spectrum of the disease or merely a more advanced stage of the disease [14], many clinicians distinguish between tremor dominant (TD) and postural instability and gait difficulty dominant (PIGD) subtypes of PD, both in terms of their clinical prognoses as well as their management [15]. FOG is predominantly seen in the PIGD subtype and has an inconsistent response to levodopa or DBS. The development of an effective treatment for FOG remains a priority in the field.

### Rationale for DBS of the mesencephalic locomotor region

The mesencephalic locomotor region (MLR) is a physiologically defined area in the midbrain tegmentum, where electrical stimulation was found to initiate locomotion in cats [16, 17]. Since its discovery in 1966, the MLR has been identified in multiple species, as a phylogenetically preserved node in the supraspinal locomotor network [18–23], with studies suggesting therapeutic potential in animal models of gait disorders [24–26]. Electrophysiological and functional imaging evidence also supported its existence in humans [27–29], encouraging clinical interest in the region as a DBS target to promote gait. Specifically, this was thought to be a potential treatment for patients with the PIGD subtype of PD [15] and FOG that did not respond to levodopa therapy or conventional DBS of the STN or GPi [30–32].

Over the past 15 years, several centers have reported on DBS of the pedunculopontine nucleus (PPN), a putative anatomical component of the MLR, for postural instability and gait dysfunction in PD [33]. Despite initially promising case reports [34, 35], the efficacy of this therapy has since been called into dispute through the results of double-blinded studies and meta-analyses [36–39].

Several reasons have been posited to explain this lack of efficacy, including potential species differences in MLR function, and the degeneration of MLR neurons in PD [40–42]. A recent clinical study of DBS assessed FOG outcomes using a responder analysis. Of the reported subjects, there was a “good responder” cluster with near resolution of percent time spent in FOG with DBS on compared to off (34.1 ±14% vs. 2.7 ±2.6%) [43]. The best responders had active electrodes in the dorsal part of the MLR in the cuneiform nucleus (CnF) rather than the PPN (Fig. 1) [43]. This aligns with recent optogenetic studies in rodents, which showed that stimulation of glutamatergic neurons in the CnF effectively and specifically caused locomotor initiation [47, 48] (For review see [46]). It also agrees with preclinical electrophysiological studies in the cat, where stimulation of low threshold sites within the MLR primarily showed CnF neuron activation [49]. The importance of electrode targeting on efficacy in this region is reinforced by computer modeling studies, demonstrating that targeting errors of 1 mm can significantly decrease target activation selectivity [50].

**Fig. 1 Fig1:**
[figure not shown]
Three-dimensional anatomy of the human MLR and expected side effects of DBS. Reconstructions were made using Lead-DBS and available MNI-space subcortical atlases [44]. A separate CnF (cyan) NIfTI object was created in relation to the PPN (dark purple) based on Olszewski and Baxter’s Atlas [45]. **A** Sagittal projection (5 mm lateral to midline) of the CnF (cyan) and PPN (dark purple) with overlay of active contacts from PPN DBS patients with poor (red), good (green), best (blue), and unevaluated (yellow) gait outcomes from Goetz et al. [43]. **B** Diagonal 3D view with right ML and STT absent to visualize the MLR, projected on to a transverse slice of the brain at the level of the pons. **C** Chart lists nearby structures, their relation to the CnF, and expected side effects of stimulation. CnF Cuneiform nucleus, CTT central tegmental tract, dSCP decussation of superior cerebellar peduncle, LC locus coeruleus, ML medial lemniscus, PPN Pedunculopontine nucleus, RN red nucleus, STT spinothalamic tract. Adapted from Fig. 2 of [46] with permission

Thus, this pilot study is designed to test the safety, feasibility, and preliminary efficacy of CnF DBS in alleviating FOG. Through this and future larger scale studies, we ultimately aim to explore the hypothesis that the CnF represents the neuroanatomic basis of the MLR and that suboptimal targeting may have played a role in the equivocal results of prior PPN DBS studies. We hope to confirm the findings in Goetz et al. [43], which suggest that minute changes in DBS target location in this area have significant impacts on clinical outcome and determine if CnF DBS may be a viable therapy for FOG and other gait dysfunctions.

## Methods/design

### Study design and overview

This study is a prospective, non-randomized, single-arm, open-label, pilot clinical trial designed to evaluate the safety and feasibility of delivering DBS to the CnF to alleviate freezing of gait in PD patients with severe, levodopa-resistant gait freezing. This study was approved by the University of Miami Human Subject Research Office (UM HSRO) and the US Food and Drug Administration with an Investigational Device Exemption as a phase I trial. The trial is registered in ClinicalTrials.gov: (NCT04218526). The study outline is shown in Fig. 2.

**Fig. 2 Fig2:**
[figure not shown]
Flow chart of study outline

Suitable eligible patients will be screened for study participation and begin the consenting process, where the study objectives and the risks and benefits of participating are explained to them. Informed consent forms for the study will be filled out by subjects to confirm enrollment and they will undergo a baseline assessment, including a thorough neurological and neuropsychiatric examination, as well as standardized subjective and objective gait assessments. The Columbia Suicide Severity Rating Scale is included during screening given the known risk of suicidality with DBS for PD [51]. After enrolment and baseline evaluation, subjects will be consented for surgery prior to bilateral implantation of DBS electrodes in the CnF, with a post-operative CT scan to localize final electrode positions. For ethical reasons, all subjects will receive active stimulation beginning at 2 weeks post-implantation and will undergo repeated gait assessments in the clinic at 2-, 6-, 12-, and 24-weeks post implantation (Table 1). Gait assessment tests will be performed on medication, with DBS on and off, and assessors will be blinded to whether the DBS is on or off to minimize the risk of bias. A more detailed kinematics and EMG gait assessment, using the Nexus system (Vicon Motion Systems Ltd) will take place at study onset and conclusion. At study conclusion, subjects will decide whether they want to continue with stimulation or discontinue stimulation; in both cases, they will continue to receive their usual standard care and follow up with their neurologist.

**Table 1 Tab1:** Detailed study schedule

Assessment	Visit 1	Visit 2	Visit 3	Visit 4	Visit 5	Visit 6	Visit 7	Visit 8	Visit 9
	Screen	Baseline assessment	Surgical screening	Surgery	2-week F/U	6-week F/U	12-week F/U	24-week F/U	25-week F/U
**Screening ICF**	X								
**Pre-op work up**^*^ **(CBC, CMP, β-hCG, INR/PTT/PT, U/A, EKG, CXR)**	X		X						
**Neuropsychiatric evaluation (including MDRS and BDI)**	X	X	X		X	X	X	X	
**Columbia Suicide Severity Rating Scale**	X	X	X		X	X	X	X	
**Gait assessment**	X	X			X	X	X	X	
**MDS-UPDRS**	X	X			X	X	X	X	
**FOG Questionnaire**		X			X	X	X	X	
**Timed Up and Go test**		X			X	X	X	X	
**Velocity test**		X			X	X	X	X	
**Variability test**		X			X	X	X	X	
**PDQ-39**		X	X		X	X	X	X	
**PDQL**		X	X		X	X	X	X	
**Brief pain history and NPSI**		X	X		X	X	X	X	
**Surgical ICF**			X						
**MRI**			X						
**Device implantation**				X					
**CT scan**				X					
**EMG analysis**		X		X					X
**Programming**					X	X	X	X	X
**Gait kinematics**		X							X

*BDI* Beck Depression Inventory, *β-hCG* Beta human chorionic gonadotropin, *CBC* complete blood count, *CMP* comprehensive metabolic panel, *CT* computed tomography, *CXR* chest x-ray, *EKG* electrocardiogram, *EMG* electromyogram, *FOG* freezing of gait, F/U follow-up, *INR* international normalized ratio, *NPSI* Neuropathic Pain Symptom Inventory, *MDRS* Mattis Dementia Rating Scale, *MDS-UPDRS* Movement Disorder Society Unified Parkinson’s Disease Rating Scale, *MRI* magnetic resonance imaging, *PDQ-39* Parkinson’s Disease Questionnaire-39, *PDQL* Parkinson’s Disease Quality of Life questionnaire, *PT* prothrombin time, *PTT* partial thromboplastin time, *U/A* urinalysis

^*^Pre-op labs are viable for 30 days before surgery. After 30 days, they must be repeated before surgical procedure

### Participants

We are actively screening and recruiting patients for this study from the Movement Disorders Clinic at the University of Miami Hospital. As this is a pilot study, we plan to enroll 4 patients with PD with levodopa-resistant FOG. A movement disorder neurologist will assess the eligibility of a patient based on the inclusion and exclusion criteria are detailed below.

### Inclusion criteria

Age 40–75FOG is the primary complaint despite optimized dopaminergic therapy by a movement disorder neurologistClinical observation of FOG in the ON/OFF states by a movement disorder neurologistPD stage 3 with good response to levodopa (defined as greater than 20% improvement in MDS-UPDRS score), except for severe gait disorderPD stage 3 with severe gait dysfunction and predominant axial symptoms defined as TD/PIGD ratio ≤ 0.90 (mean value of MDS-UPDRS items 2.10, 3.15a, 3.15b, 3.16a, 3.16b, 3.17a, 3.17b, 3.17c, 3.17d, 3.17e, and 3.18 divided by the mean value of MDS-UPDRS items 2.12, 2.13, 3.10, 3.11, and 3.12) [15] and FOGQ score> 12Minimal tremor, bradykinesia, and rigidity, or well controlled with levodopa.Agrees to full 6-month study participation

### Exclusion criteria

Individuals with major executive dysfunction, dementia (Mattis Dementia Rating Scale-2 score ≤ 130), depression (Beck Depression Inventory II ≥ 25), or other neurocognitive impairmentsPresence of major medical co-morbidities and other surgical contra-indicationsIndividuals requiring diathermy, transcranial magnetic stimulation, or electroconvulsive therapyIndividuals with prior intracranial surgeryIndividuals with non-MRI compatible metallic implants in their head or active implantable devices anywhere in the bodyIndividuals who are pregnant, breastfeeding, or the desire to become pregnant during the studyIndividuals on investigational drugs or any other intervention (not part of the guidelines for management of PD) known to have a potential impact on outcome

### Assessments

The following assessments will be completed to screen for study/surgical eligibility:
History and physical exam, including a neurological and clinical gait assessmentBlood pressure and postural dropPre-operative lab work, including 12-lead electrocardiogram and chest x-rayNeuropsychiatric evaluation, including the Mattis Dementia Rating Scale-2, Beck Depression Inventory II, and the Columbia Suicide Severity Rating Scale

The following assessments will be completed prior to DBS implantation as well as at each clinic visit post-implantation:
MDS-UPDRSFOG QuestionnaireTimed Up and Go (TUG) testInstrumented gait assessment (Opal Inertial measurement unit, APDM Inc., Portland, OR) measuring:
Stride length (average over 2-min walk)Velocity (average over 2-min walk)Gait variability (measured over a 2-min walk)360° clockwise and counterclockwise turn on the spot (time and number of steps)The Parkinson’s Disease Questionnaire (PDQ-39) and the Parkinson’s Disease Quality of Life Questionnaire (PDQL)Columbia Suicide Severity Rating ScaleA brief pain history and Neuropathic Pain Symptom InventoryBlood pressure and postural drop assessed in the off and on DBS stimulation state.

At study conclusion, patients will undergo a detailed kinematics gait assessment using the Nexus system (Vicon Motion Systems Ltd) and surface EMG recordings in the lower limbs.

### Device implantation

The Vercise™ (Boston Scientific Corporation) DBS System and Cartesia™ (Boston Scientific Corporation) directional leads will be used in this study. Implantation of electrodes and generator will be performed in one procedure, as previously described at our institution [52] but targeting the CnF. A pre-operative 3T MRI will be obtained prior to surgery. Subjects will be admitted on the day of surgery, and under intravenous sedation, a CRW frame will be placed and a CT obtained. The CT and MRI will be merged to obtain frame-based coordinates for the CnF. The default CnF coordinates will be calculated based on MRI brainstem landmarks to target brainstem normalized coordinates of (0.50, 0.25, 0) [43], and diffusion tractography will be used to ensure that our target is within the area demarcated by the medial lemniscus, superior cerebellar peduncle, and central tegmental tract. Trajectory planning will be performed to avoid vessels and ependymal and pial surfaces. Blood pressure and heart rate will be monitored by arterial line, and systolic blood pressure will be maintained between 90 and 120 mmHg during electrode insertions to reduce the risk of hemorrhage. The DBS lead placements will be preceded by microelectrode recordings and test stimulations to assess intraoperative physiology and rule out potential side-effects that may warrant repositioning of the lead (Fig. 1C). Intraoperative lower-extremity EMG will be used to assess for muscle activation to assist with targeting, as has been noted in animal studies targeting the CnF [49, 53]. If no such changes are noted, the lead positioning is determined only by target coordinates and avoiding side effects of stimulation. The use of an intraoperative O-arm (Medtronic) spin to provide real-time estimates of lead trajectory and location will be an option if there are any concerns about targeting or off-target stimulation effects. After implantation, patients will be fully anesthesized to undergo subcutaneous implantation of the generator in the chest to complete the procedure. Patients will be admitted to a post-surgical unit overnight for monitoring, including blood pressure and vital signs.

### DBS programming

Intraoperative stimulation parameters will be used to guide initial programming. Programming sessions will have heart rate, blood pressure, respiratory rate, and blood oxygenation saturation monitoring to mitigate the risk of adverse cardiorespiratory events related to stimulation. Additionally, low frequencies will initially be explored with patients until an adequate stimulation amplitude is found where gait initiation is under volitional control. Stimulation amplitude will then be increased until an adequate gait speed is achieved. If this is not immediately apparent, stimulation amplitude will be increased to just below the threshold for onset of side effects. Based on other studies, cyclic stimulation with continuous daily stimulation and night arrests will be the default protocol to avoid habituation and waning of effects [43, 54]. Current steering will be used to increase the therapeutic window and maximize chances of therapeutic benefit.

### Safety and feasibility

The analyses for safety will be descriptive, focusing on trends for within-subject differences and changes in FOG symptoms or off-target side-effects during the duration of the study. All adverse events (AEs) will be listed and their incidence compared to historical controls. The primary safety analysis will be conducted on all patient data when all 4 participants have completed the study.

### Endpoints of safety and feasibility

DeathOccurrence of pre-defined stoppage rulesSuccessful implantation and complete follow-up of 4 patients

Outcomes of neurological and functional status, gait, and quality-of-life are collected at several time points during the study (Table 1).

### Secondary outcomes

Percent change in FOG Questionnaire (FOGQ), Parkinson’s Disease Questionnaire (PDQ-39), and the Parkinson’s Disease Quality of Life Questionnaire (PDQL)Percent change in Movement Disorders Society Unified Parkinson’s Disease Rating Scale (MDS-UPDRS) Part III across study visits relative to pre-operative baseline evaluation.Percent change in number of falls (between baseline and final gait testing sessions, and on item 13 of UPDRS III)Percent change in gait velocity with and without CnF DBSPercent change in muscle electromyogram (EMG) amplitude during gait testing at study conclusion between CnF DBS on and off conditions

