### Data analysis

The primary goal of this pilot study is to assess the safety and feasibility of delivering DBS to the CnF in PD patients with refractory FOG and thus will only involve 4 subjects. We believe this number of subjects will provide adequate data on safety and feasibility for a larger study. However, assessment of trend toward efficacy will be performed for the secondary outcomes. One-way ANOVA will be used to compare percent improvement in gait velocity for the four different DBS configurations (L CnF off/R CnF off, L CnF off/R CnF on, L CnF on/R CnF off, L CnF on/R CnF on) at each clinic visit, with the Tukey Honest Significant Difference post hoc test to compare configurations. The same test will be used to compare changes in EMG amplitude between the four DBS configurations at the final gait assessment at the study’s conclusion. One-way ANOVA with repeated measures will be used to compare changes in the UPDRS III, FOG Questionnaire, PDQ-39, and PDQL over the multiple time points of the study.

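### Only one pre-operative FOGQ is scheduled, so unless an unscheduled earlier score qualifies the patient, the score tested against the cut-off is also the baseline and regression to the mean reads as improvement

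*Protocol article*

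**What the plan says.** All places are in the Protocol article.

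- **Inclusion criteria.** A FOGQ score above 12 is required, within the criterion on severe gait dysfunction and predominant axial symptoms.
- **Table 1.** The row "FOG Questionnaire" is marked at Visit 2 (baseline assessment) and at Visits 5 to 8 (2, 6, 12 and 24 weeks). It is not marked at Visit 1 (screen) or Visit 3 (surgical screening). The MDS-UPDRS is marked at Visits 1 and 2; the PDQ-39 and PDQL are marked at Visits 2 and 3.
- **Assessments.** The FOGQ is in the list introduced by "The following assessments will be completed prior to DBS implantation as well as at each clinic visit post-implantation". It is not in the list introduced by "The following assessments will be completed to screen for study/surgical eligibility".
- **Secondary outcomes.** The first item begins "Percent change in FOG Questionnaire (FOGQ". The phrase "across study visits relative to pre-operative baseline evaluation" is attached to MDS-UPDRS Part III; no reference point is stated separately for the FOGQ.
- **Data analysis.** "One-way ANOVA with repeated measures will be used to compare changes in the UPDRS III, FOG Questionnaire, PDQ-39, and PDQL" over the study's time points.
- **Study design and overview.** The trial is a "prospective, non-randomized, single-arm, open-label, pilot clinical trial". Blinded DBS on/off comparison is described for the gait tests. Secondary outcomes has with/without or on/off contrasts for gait velocity and EMG, but none for the FOGQ.

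**The concern.** A score kept because it exceeds a cut-off carries, on average, some upward error. The next score from the same patient lacks that selected error, so it tends to be lower even if nothing has changed. If the qualifying score is also the reference for change, the drop is counted as improvement. Four post-operative scores do not dilute it, because the error sits in the one reference they share.

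In a randomised trial the control arm would show the same drop and subtract it. Here nothing does. The FOGQ is the only freezing-specific questionnaire in the plan, and the secondary outcomes will be read for a trend toward efficacy in a pilot meant to support larger trials. An artefact that always points toward benefit could therefore colour that decision.

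**Working it through.** **1. Is there a figure in the plan to reproduce?** No. The article gives no FOGQ mean, SD, reliability or expected effect, and the sample of four is set by the pilot aim rather than by calculation.

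**2. Inputs.** From the article: cut-off above 12, one scheduled pre-operative score, four patients, one arm. Assumed: candidate mean μ = 10–16, SD σ = 3–5, reliability (test-retest correlation) ρ = 0.6–0.9, integer scores from 0 to 24, and no treatment effect.

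**3. Formula.** For selection above a cut-off, with 12.5 as the continuity cut for integer scores above 12:

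- a = (12.5 − μ)/σ and λ = φ(a)/(1 − Φ(a))
- mean baseline of those selected = μ + σλ
- expected fall at the next score = (1 − ρ)σλ

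Worked case, μ = 13, σ = 4, ρ = 0.8: a = −0.5/4 = −0.125 and λ = 0.720. Baseline = 13 + 4 × 0.720 = 15.88. Fall = 0.2 × 4 × 0.720 = 0.58 points, and 0.58/15.88 = 3.6%.

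**4. Across the assumed range.** The formula columns give the fall and that fall as a share of mean baseline. The last two columns come from simulation with rounded scores bounded at 0–24: the mean of individual percent changes, and the chance that the mean percent change of four patients is an improvement of 10% or more.

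| μ, σ, ρ | Baseline | Fall (points) | Fall/baseline | Simulated mean % change | Four-patient mean improves ≥10% |
|---|---|---|---|---|---|
| 16, 3, 0.9 (mildest) | 16.69 | 0.07 | 0.4% | −0.2% | 1% |
| 13, 4, 0.8 | 15.88 | 0.58 | 3.6% | −3.4% | 20% |
| 12, 4, 0.75 | 15.52 | 0.88 | 5.7% | about −5% | 30% |
| 12, 5, 0.75 | 16.31 | 1.08 | 6.6% | about −6% | 36% |
| 10, 5, 0.6 (largest) | 15.71 | 2.28 | 14.5% | −14.1% | 62% |

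**5. How much of the last column is selection?** With four patients, a 10% mean improvement also arises from ordinary noise. Repeating the two μ = 12 cases with a separate pre-operative score as baseline still gives about 12% (σ = 4) and 15–16% (σ = 5). The excess due to using one score twice is therefore roughly 30 − 12 = 18 and 36 − 16 = 20 percentage points, not the full 30–36%.

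**6. Effect of a separate baseline.** With qualifying and baseline scores separated, the simulated expected change in points is about 0 in every case run.

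**The case against.** The strongest reply is that no sentence in the article says the Visit 2 score decides eligibility. Study design and overview describes eligible patients being screened, consent forms confirming enrolment, and baseline assessment following. Participants has a movement disorder neurologist judge eligibility. A clinic FOGQ could have been taken before Visit 2, in which case Visit 2 is already the separate baseline. This stands: a reader might infer that the Visit 2 score must serve both purposes, and the document does not establish that. It establishes only that no other pre-operative FOGQ is scheduled.

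A reader might also take the FOGQ's absence from the eligibility list in Assessments as proof. It is not. The MDS-UPDRS is missing from the same list, although it defines entry criteria and is scheduled at Visit 1, so the list is not exhaustive.

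On size, the entry criteria also demand FOG as the primary complaint, observed FOG and severe gait dysfunction. These may select patients well above 12, where the artefact nearly vanishes. That stands too, and is why only a range can be given. A suggestion that patients score high to obtain the implant has no support in the document.

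Finally, the FOGQ is one of several secondary outcomes, the Discussion concedes the small sample and the lack of a control cohort, and open-label expectation would affect a self-report whatever the baseline. All true. But that general concession does not mention this mechanism, which, unlike a missing control arm, can be removed cheaply.

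**Conclusion.** The point holds conditionally. On the written schedule only one pre-operative FOGQ exists to meet the cut-off and to anchor the change. That Visit 2 is the FOGQ reference is itself inferred from its being the only such score. Unless an unscheduled earlier score is used for eligibility, part of any FOGQ improvement will be regression to the mean, always toward benefit.

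The size rests wholly on assumed inputs: negligible if candidates score well above 12 and the scale is highly reliable, and about 14% at the unfavourable end. The document does not support a claim that the bias is large, nor reading the 30–36% chance of a 10% improvement as the size of the flaw, since 12–16% remains with a separate baseline. Safety and feasibility conclusions are untouched. This is a worthwhile, inexpensive improvement that protects the efficacy-trend reading.

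**What to change.** In Table 1, add the FOGQ at Visit 1 and state that the cut-off is applied to that score only. Name the separate Visit 2 score as the baseline for FOGQ change in all patients, and do not apply the cut-off to it again.

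For any patient already qualified on the Visit 2 score, report the FOGQ change with that limitation stated. If a repeat pre-operative score is taken, show it as a sensitivity analysis; making it the baseline for some patients would give four patients two baseline definitions. If eligibility has in fact been judged on an earlier clinic score, say so and show it in Table 1.

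Report the change in points beside the percent change. The separate baseline centres the expected point change on zero, whereas a mean of individual percentages still depends on a noisy denominator.

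Cost: one extra short form at an existing visit and one table entry. The baseline will probably be slightly lower, with some patients possibly at or below 12, so the stated improvement will look less favourable. The noise from having four patients remains.
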